### Outcome measures

#### Primary outcome

The primary outcome is the proof of BST's superiority compared with placebo in treating FD. For this purpose, the GIS scale is chosen as the primary variable [1]. The primary efficacy parameter is the change in the sum totals of the GIS scales. The GIS scale is composed of the following 10 dyspeptic symptoms: epigastric pain/upper abdominal pain, abdominal cramps, fullness, early satiety, loss of appetite, malaise, nausea, vomiting, retrosternal discomfort, and acidic regurgitation/heartburn. Symptom severity per each item will be assessed by a 5-point Likert scale: none - 0, slight - 1, moderate - 2, severe - 3, and very severe - 4. The GIS scale is very easy for participants to understand and to complete. The GIS scale will be assessed at baseline, 2 weeks, 4 weeks and 6 weeks during oral administration of BST, and at 1 month and 2 months after completion of BST administration.

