### Statistical analysis

The primary hypothesis is that oral administration of BST is more effective than placebo for treating FD. We hope to prove this hypothesis by means of a 2-sided test yielding a 5% significance level. Because there is no relevant previous study using BST for calculating sample size, we referred to a similar herbal trial for FD treatment which used the GIS scale [1]. The formula for estimating the sample size is as follows:

The previous trial demonstrated 3.5 points of improvement (*μ*_*c *_- *μ*_*t *_= *Δ*) in the GIS scale over treatment with placebo during 4 weeks of herbal treatments [1]. The same study indicated a mean standard deviation (SD = *σ*) of 5.37. In our study, the ratio (*λ*) of experimental group to placebo group will be 1:1. With a power of 80% (1 - β) and significance level of 5% (α), assuming Δ = 3.5 and σ = 5.37, a sample size of *n_t _*= *n_c _*= 37 patients per treatment group will be required. (*n_t_*, number of BST group; *n_c_*, number of placebo group). Considering an assumed dropout rate of 25%, a total of 100 patients will be needed.

The analysis strategy in this study is as follows:

As a first step, the baseline characteristics of both groups, sex, age, duration of dyspeptic periods, and smoking, will be compared. As a second step, we will compare the efficacy of BST and placebo, as the change in GIS totals from the beginning (0 day) to the end (6 weeks) of the study period. As a third step, we will analyze the secondary variables (VAS and FD-QoL) in the same manner as we did the GIS scale. Finally, various parameters in the EGG measurement, such as frequency and power-related variables will be compared before and after treatment in both groups. Correlations between changes in GIS scale results and EGG parameter findings will also be analyzed.

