All analyses in this study will be based on the intention-to-treat principle. If data distribution is skewed owing to insufficient sample size, relevant transformation by a statistician prior to analysis will be made. The baseline characteristics will be compared by either *χ*^2^-test or the Student *t*-test. Primary and secondary outcomes will be presented as means and SDs, and analyzed by independent *t*-tests, Mann-Whitney tests, or Wilcoxon singed-rank tests. Correlations between the GIS scale and EGG parameters will be analyzed by Pearson's correlation coefficients or by Spearman's Rho. Adverse events will be calculated and compared using *χ*^2^-test or Fisher's exact test.

Statistical analyses will be conducted in a blind manner by an independent statistician and performed using SPSS 16.0 (SPSS inc., Chicago, Illinois, USA).

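### The 80% power holds for about 37 evaluable patients per arm and is not linked to the declared intention-to-treat analysis; a baseline-adjusted repeated-measures model would serve that analysis better

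*Protocol article*

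**What the plan says.** All references are to the protocol article.

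- **Sample size (Statistical analysis).** The hypothesis is to be tested "by means of a 2-sided test yielding a 5% significance level". The calculation runs at 80% power, "assuming Δ = 3.5 and σ = 5.37", with equal arms, and concludes that "37 patients per treatment group will be required". It then adds: "Considering an assumed dropout rate of 25%, a total of 100 patients will be needed".
- **Primary comparison (Statistical analysis).** The arms are compared on the change in GIS total between day 0 and week 6.
- **Population and tests (Statistical analysis).** "All analyses in this study will be based on the intention-to-treat principle". The tests listed for primary and secondary outcomes are the independent t-test, the Mann-Whitney test and the Wilcoxon signed-rank test.
- **Data collected (Primary outcome).** "The GIS scale will be assessed at baseline, 2 weeks, 4 weeks and 6 weeks during oral administration of BST". Two post-baseline scores are therefore planned for each patient before the primary time point.

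**The concern.** Dividing by 0.75 counts a quarter of the randomised patients as adding nothing to the primary comparison. An intention-to-treat analysis is meant to include them. The power of such an analysis depends on the treatment difference among those who leave, and the calculation does not consider that.

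The listed tests add to the problem. A t-test or rank test of a single change score needs one week-6 value per patient. It cannot draw on the week-2 and week-4 scores of someone who has left unless a separate step fills in the missing value. It also takes no account of baseline GIS, which usually predicts later GIS. The signed-rank test is a paired test and does not compare the arms.

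Two things are at stake. The stated 80% may be too high or too low for the analysis that is declared. And in a trial that expects to lose 25% of its patients, the named method uses the collected data inefficiently and relies more than it needs to on those who finish.

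**Working it through.** **Inputs from the article:** Δ = 3.5 GIS points; σ = 5.37; two-sided α = 0.05; power 80%; 1:1 allocation; dropout 25%.

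**Step 1. Reproduce the plan's figures.**
n per arm = 2(1.960 + 0.842)² × 5.37² / 3.5² = 36.95, so 37.
37 / (1 − 0.25) = 49.3, so 50 per arm and 100 in total. Both figures agree with the article.
Power at 37 per arm is 80.0% by the normal approximation and 79.0% by the noncentral t distribution. The stated 80% is thus the power with about 37 evaluable patients per arm.

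**Step 2. Power when all 50 per arm are analysed.**
Let r be the share of the 3.5-point effect that dropouts keep. This is an assumption; the article gives no value. The average difference is 3.5 × (0.75 + 0.25r), with SD held at 5.37.

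| r | Difference | Power, noncentral t | Power, normal |
|---|---|---|---|
| 0 | 2.625 | 67.7% | 68.6% |
| 0.5 | 3.0625 | 80.6% | 81.4% |
| 1 | 3.5 | 89.7% | 90.3% |

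Power reaches 80% at a difference of 3.04 points, r about 0.47 (noncentral t), or 3.01 points, r about 0.44 (normal). At r = 0, 80% power would need 2(1.960 + 0.842)² × 5.37² / 2.625² = 65.7, so 66 per arm or 132 in total.

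**Step 3. How firm is the lower end?**
Step 2 keeps the SD fixed. A fill-in rule can also change the spread. If dropouts are given a change of zero (baseline carried forward), the variance in an arm with mean completer improvement m is 0.75 × 5.37² + 0.75 × 0.25 × m². The difference is 2.625. With an assumed placebo improvement of 0 points, the standard error is √[(21.63 + 23.92)/50] = 0.954 and power is 79% (normal). With an assumed 8 points it is √[(33.63 + 46.42)/50] = 1.265 and power is 55%. The article fixes no such rule, so this only shows that 68% is not a floor under every rule.

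**Step 4. What baseline adjustment could gain.**
Suppose GIS has equal variance at baseline and week 6, with correlation ρ (assumed). Adjusting for baseline multiplies the variance of the change-score comparison by (1 + ρ)/2. At 37 per arm the unadjusted standard error is 5.37 × √(2/37) = 1.25.
- ρ = 0.35: 1.25 × √0.675 = 1.03.
- ρ = 0.70: 1.25 × √0.85 = 1.15.

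A simulation of the full repeated-measures model with change SD held at 5.37, assumed visit correlations and a true difference of 3.5 points the arms the same way. The standard error fell from about 1.23 (completer t-test) to 1.02–1.06. The model's estimate was about 3.5, against 3.3–3.45 for completer analyses. These figures depend on assumed correlations and an assumed dropout pattern; the article supplies neither.

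**The case against.** The strongest reply is that nothing here is wrong. Inflating for dropout while declaring intention-to-treat is ordinary practice, and the arithmetic reproduces. A t-test or Mann-Whitney test can be run on every randomised patient once a rule for missing week-6 values is applied. Such a rule is commonly left to the full protocol or analysis plan, neither of which is shown, and it might use the week-2 and week-4 scores. The article also does not say that GIS collection ends when treatment stops, or who is likely to leave.

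Most of this stands, and it rules out three stronger readings:

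- **A reader might infer that intention-to-treat and 80% power cannot both hold.** They can, whenever dropouts keep roughly 44–47% or more of the effect.
- **A reader might infer that the plan is a completer analysis under another name.** The article nowhere excludes dropouts, and the absence of a printed missing-data rule is not a finding.
- **A reader might infer that a completer t-test falls well short of 79%.** That follows mainly from treating 5.37 as the SD of a single score. At an assumed correlation of 0.35 the change SD would then be 5.37 × √(2 × 0.65) = 6.12. The article applies 5.37 to the improvement that is compared, and with the change SD held there the simulated power is 78–80%.

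The reply leaves two things untouched. The 80% was derived for a different set of patients from the one to be analysed. And the tests the article does name are unadjusted and do not themselves use the interim scores.

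**Conclusion.** The point holds in a limited form. The 80% is justified for about 37 evaluable patients per arm. For the declared analysis of 50 per arm, power is about 68% to 90% with SD held at 5.37, depending on how much of the effect the assumed 25% dropouts retain. The range straddles 80%, so the plan is neither shown to be underpowered nor shown to be adequate; the two statements are simply not linked.

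Separately, the named two-group tests leave baseline GIS and the week-2 and week-4 scores unused, and a standard alternative uses both. The size of that gain rests on assumed correlations. Bias from symptom-related withdrawal is plausible, because other dyspepsia drugs are barred during treatment (Design section), but the article does not establish it. This is a worthwhile, inexpensive improvement to the primary analysis, not a defect that invalidates the trial.

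**What to change.** 1. **Primary analysis.** Fit a repeated-measures model to GIS at weeks 2, 4 and 6 in all randomised patients with at least one post-baseline score. Include arm, visit, arm × visit, baseline GIS × visit and centre. The week-6 contrast between arms is primary. Report by arm the number of patients with no post-baseline score, since the model cannot include them.
2. **Sensitivity analysis.** Add one reference-based analysis in which patients who drop out of the Banha-sasim-tang arm are assumed to follow the placebo course afterwards. The model in item 1 assumes that data are missing at random; this shows how far the result depends on that.
3. **Power statement.** Say that the 80% applies to about 37 evaluable patients per arm, and give the intention-to-treat range of about 68–90% with its assumptions (25% dropout, SD 5.37, share of the effect kept from none to all).

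**Cost:** slightly more analysis work and a less favourable lower bound on the stated power. No additional patients, visits or measurements are required.

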### Safety

Before randomization and after completion of BST administration, we will perform the following tests on all participants: complete blood cell count, AST/ALT, γGT, BUN, creatinine, erythrocyte sedimentation rate as well as electrocardiogram. The above tests will serve to exclude participants who have serious illnesses and abnormal heart, liver, kidney, or other organ functioning. Throughout the study, we will also assess whether 6 weeks of BST administration in FD patients is safe by above tests or CRF documentations.

The guide for taking BST which are verified by the Korean Food & Drug Administration lists several adverse events: pseudoaldosteronism, myopathy, skin disorders, liver malfunction, pneumonia, or dry mouth. During the trial, all adverse events will be observed in detail and documented in case report forms (CRFs).

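### Intention-to-treat is prescribed for every analysis, including adverse events, which slightly understates any excess harm among patients who took BST (minor)

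*Protocol article*

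**What the plan says.** The protocol article, Statistical analysis, sets one rule for the analysis population: "All analyses in this study will be based on the intention-to-treat principle". The same paragraph then lists the tests for baseline characteristics, primary and secondary outcomes, and correlations. It ends the list with safety: "Adverse events will be calculated and compared using" a chi-square or Fisher's exact test. No treated population is named, and no exception is made for safety.

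The Safety section frames the question by exposure: "we will also assess whether 6 weeks of BST administration in FD patients is safe by above tests or CRF documentations". It also says of the blood tests and electrocardiogram that "we will perform the following tests on all participants", which says who is tested but does not define an analysis set. The Abstract gives 50 patients per group.

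**The concern.** For the superiority claim on the GIS total, intention-to-treat is generally the cautious choice, because it tends to pull the arms together and so works against the claim. The same pull is not cautious for harm. A patient who never took the granules cannot have been harmed by them, yet would add to the denominator. A placebo patient who received BST by mistake would add any BST-related event to the placebo arm. Where BST does raise the event rate, both make the excess look smaller.

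The trial is meant to provide evidence on safety as well as efficacy, and the Safety section lists labelled risks such as liver malfunction and myopathy. The population rule for that part should not lean towards finding no difference.

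**Working it through.** **The plan's own figure.** The inputs are "a power of 80% (1 - β) and significance level of 5% (α), assuming Δ = 3.5 and σ = 5.37" and 1:1 allocation, all from Statistical analysis.

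- n per group = 2 × (1.960 + 0.8416)² × 5.37² / 3.5² = 2 × 7.849 × 28.837 / 12.25 = 36.95, rounded up to 37 as stated.
- With 25% dropout: 37 / 0.75 = 49.3, so 50 per group and 100 in total, as stated.

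The sample size reproduces and is not affected by this point.

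**Inputs for the safety check.** From the article: 50 randomised per arm, and adverse events compared by a chi-square or Fisher's exact test. Assumed, because the article gives no values: true event rates in treated patients of 20% on BST and 5% on placebo, and 1, 3 or 5 deviating patients per arm.

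**Formulas.** Let p₁ and p₀ be the true rates on BST and placebo, and u the share of deviating patients in each arm.

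- Non-starters with no events: the rates become p₁(1 − u) and p₀(1 − u). The difference becomes (p₁ − p₀)(1 − u), and the ratio stays p₁/p₀.
- Swapped products: the rates become p₁(1 − u) + p₀u and p₀(1 − u) + p₁u. The difference becomes (p₁ − p₀)(1 − 2u), and the ratio falls.

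| Deviation per arm of 50 | BST, by assignment | Placebo, by assignment | Risk difference (points) | Risk ratio |
|---|---|---|---|---|
| None | 20.0% | 5.0% | 15.0 | 4.00 |
| 1 non-starter | 19.6% | 4.9% | 14.7 | 4.00 |
| 3 non-starters | 18.8% | 4.7% | 14.1 | 4.00 |
| 5 non-starters | 18.0% | 4.5% | 13.5 | 4.00 |
| 1 swapped | 19.7% | 5.3% | 14.4 | 3.72 |
| 3 swapped | 19.1% | 5.9% | 13.2 | 3.24 |

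Grouping treated patients by product taken restores 20% v 5% in every row.

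**Other assumed rates.** At 10% v 2%, the difference falls from 8.0 to 7.84 points with one non-starter per arm and to 7.2 with five. At 30% v 10%, it falls from 20.0 to 19.6 and 18.0.

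**If non-starters have background events.** Suppose they report events at the placebo rate instead of none. With one per arm, BST shows 0.98 × 20 + 0.02 × 5 = 19.7% and placebo 5.0%. The difference is again 14.7 points, but the ratio slips to 19.7 / 5.0 = 3.94.

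**Power at 20% v 5%, intention-to-treat v treated set.** With three non-starters per arm, it is 0.593 v 0.597 by the normal approximation and 0.468 v 0.468 by exact enumeration of Fisher's test. With five, it is 0.572 v 0.578 and 0.440 v 0.480. The Fisher gap appears only at five; with one, two or three non-starters the two sets give the same power.

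**The case against.** The strongest reply is that a journal article condenses the full protocol. Analysis sets are commonly defined elsewhere, and the article neither defines intention-to-treat nor says that never-dosed patients enter the adverse event denominator. That would answer a complaint about silence. Here the article states a general rule and lists the adverse event test under it, so a treated safety set in an unseen SAP would depart from the published sentence.

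The reply on size largely stands. Nothing in the article reports or anticipates non-starters or dispensing errors, and with a few such patients the comparison hardly changes.

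Four stronger readings are tempting, and the article does not support them:

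- A reader might infer that events rather than patients are tabulated, which would make the p-value too small. The article does not say so, and its two tests are the usual ones for patients with and without an event.
- A reader might take the 25% dropout as a guide to non-starting. It is not one: a patient who takes a dose and then withdraws belongs to both sets.
- A reader might say that one mis-dispensed patient moves a rate by 2 points (1 of 50). That holds only if the patient has an event. In expectation, one placebo patient given BST makes the placebo rate (49 × 5% + 20%) / 50 = 5.3%, a shift of 0.3 points.
- A reader might extend the dilution to the laboratory tests and electrocardiogram. The general sentence reaches them, but the article names no test for them and schedules the second measurement after treatment is completed, so dilution there is not shown.

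**Conclusion.** The point holds as a minor one. On its plain wording the intention-to-treat rule covers the adverse event comparison, although the safety question concerns patients given BST. The effect depends on non-starters or wrongly supplied patients actually occurring.

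Under balanced non-starting, the risk difference is understated by the share u: 2% of its value with one patient per arm of 50, and 10% with five. The risk ratio is untouched if those patients report no events. Swapped products lower the ratio as well. The direction favours BST only where BST truly has the higher event rate, and unbalanced non-starting could distort the comparison in other ways. All event rates and patient counts used here are assumptions. The rule does not show that the safety conclusion would be wrong.

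**What to change.** Limit the intention-to-treat sentence to the efficacy analyses. Add that adverse events will be compared among randomised patients who took at least one dose, grouped by the product actually taken. Settle this before unblinding, so that the safety set is not chosen with the results in view.

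The cost is a change of wording. The sample size stays at 100. Reported event rates may be slightly higher, and the safety set may differ from the randomised set by a few patients, so the report would need to state both denominators.

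### The plan lists a paired signed-rank test for the primary outcome, which cannot compare BST with placebo, and ties transformation to a wrong idea of skewness

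*Protocol article*

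**What the plan says.** The Primary outcome section of the protocol article sets the aim as superiority of BST over placebo, with the change in the summed GIS scale as the efficacy parameter. The Statistical analysis section makes this a comparison of the two arms on the change in GIS total between day 0 and week 6. It adds: "We hope to prove this hypothesis by means of a 2-sided test yielding a 5% significance level". The trial is sized as a two-sample comparison of means, "assuming Δ = 3.5 and σ = 5.37", and "Considering an assumed dropout rate of 25%, a total of 100 patients will be needed".

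The next part of that section turns to method. On the scale of analysis it says: "If data distribution is skewed owing to insufficient sample size, relevant transformation by a statistician prior to analysis will be made". It gives no criterion for skewness and names no transformation. For the primary and secondary outcomes it lists independent t-tests, "Mann-Whitney tests, or Wilcoxon singed-rank tests" (the spelling is the article's), with no rule for choosing. It closes by saying that an independent statistician will do the analyses blind.

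Before-after comparisons are planned for the electrogastrography (EGG) parameters. These are not among the outcomes labelled primary (GIS) or secondary (VAS and FD-QoL).

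**The concern.** Two things are stated wrongly, and a third is left loose.

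- **Signed-rank test.** It is a paired or one-sample test. Applied to GIS change, it asks whether scores moved from baseline within one arm. Placebo patients may also improve, so a significant result in the BST arm says nothing about superiority. The Hypothesis section words the symptom claim without a comparator, so a within-arm result could be taken to satisfy it.
- **Transformation sentence.** Skewness is a property of the variable. A small sample weakens the normal approximation for the mean, but it does not make data skewed. Transforming the outcome also replaces the quantity on which the trial was sized.
- **Choice among tests.** A single two-sided 5% test is promised, but several routes are open. Whether that costs anything depends on how the choice is made.

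**Working it through.** **1. Reproduce the sample size.** Inputs from the Statistical analysis section: Δ = 3.5, σ = 5.37, two-sided α = 0.05, power 80%, ratio 1:1.

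n per group = 2 × [σ(1.960 + 0.842)/Δ]² = 2 × [5.37 × 2.802/3.5]² ≈ 36.95, rounded up to 37. With 25% dropout, 37/0.75 = 49.3, so 50 per group and 100 in total. Both stated figures are reproduced. An exact t calculation gives 37.94 per group and a power of 79.0% at 37, an immaterial difference. The sizing therefore already assumes a between-group comparison of means on the raw GIS scale.

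**2. Signed-rank test read as efficacy.** Assume no BST-placebo difference, the same mean improvement μ in both arms, within-arm SD of change 5.37 and 37 per arm. The article gives no expected placebo change, so μ is an assumption and is varied. Simulated integer-rounded normal changes, 2,000 runs per row:

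| μ (points) | BST arm significant in the direction of benefit | BST significant, placebo not |
|---|---|---|
| 1 | 19% | 16% |
| 2 | 57% | 24% |
| 3.5 | 96% | 3% |
| 5 | 100% | 0% |

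A hand check uses a relative efficiency of 0.955 against the t-test. The signal is μ × √(37 × 0.955)/5.37 = 1.107μ, and power is about Φ(1.107μ − 1.960). This gives Φ(−0.853) = 20%, Φ(0.254) = 60% and Φ(1.914) = 97% for μ = 1, 2 and 3.5, close to the simulation.

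**3. Choice between t, Mann-Whitney and a transformed t-test.** Simulated under the null with mean change 3.5, SD 5.37, normal and gamma-skewed changes, 37 and 50 per arm and 10,000 runs per setting (Monte Carlo standard error about 0.2 points):

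| Rule | Type I error |
|---|---|
| t-test, fixed in advance | 4.7% to 5.2% |
| Mann-Whitney, fixed in advance | 4.5% to 5.0% |
| Shapiro-Wilk at 5%, then t or Mann-Whitney | 4.5% to 5.2% |
| Smaller p of t and Mann-Whitney | 5.6% to 6.5% |
| Smallest p of t, Mann-Whitney and log-t on shifted scores | 6.6% to 7.2% |

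Across all settings, including smaller 2,000-run cells, the last row reached at most 7.6%. A separate run of 4,000 trials applied Shapiro-Wilk to the pooled blinded data and gave 4.3% to 4.9%.

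**4. Transformation and the sized contrast.** Ten items scored 0 to 4 give a total of 0 to 40, so the change can lie between −40 and +40. A log or square root would need an added constant, and the result would depend on that constant. Other transformations accept negative values, and the article names none. Under any nonlinear choice, the arm difference is no longer a difference in mean GIS points, and Δ = 3.5 has no direct counterpart.

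**The case against.** The strongest defence has four parts.

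- **Blinding.** A reader might infer that the open list inflates type I error as it stands. The article does not support that. It places transformation before analysis and has the analysis done blind, and a shape-based choice keeps the error near 5%. Picking the smallest p-value is nowhere described. This part stands. One reservation: the Randomization section has a statistician working from the allocation sequence, and the article does not say whether that person is also the analyst. This leaves the safeguard unclear but does not show that it fails.
- **Intent.** A reader might also infer that the plan means to count a within-arm result as proof of efficacy. It does not say so; the primary comparison is clearly BST against placebo. The signed-rank test may have been meant for within-group description or the EGG comparisons. That is plausible, but the sentence names the primary and secondary outcomes, so the listing is wrong as written.
- **Article scope.** A selection rule and a named transformation can be left to a fuller document. Their absence alone is no finding. The signed-rank listing and the skewness premise are different, because the article states both.
- **Power.** Mann-Whitney with near-normal data costs little: 77.1% against 79.0% for the t-test at 37 per arm, on the same exact basis. Power is no argument here.

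**Conclusion.** The point holds in a limited form. The plan lists, for its primary outcome, a test that cannot address its primary hypothesis. It justifies transformation by a wrong premise, and any such transformation would detach the analysis from the 3.5-point difference used for sizing.

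The signed-rank harm is conditional on a within-arm result being presented as efficacy. Its size (19% to 96% for 1 to 3.5 points at 37 per arm) rests on the assumed common improvement and on 5.37 being the SD of change. Type I inflation from the between-group choice is modest (about 6% to 7%) and arises only if the choice follows the p-value. Nothing here calls the sample size into question.

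**What to change.** Make these changes in the Statistical analysis section before unblinding:

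- Name one between-group primary analysis of the untransformed 6-week GIS total. A linear model adjusted for baseline GIS is preferable: baseline is already collected, and the model gives the same treatment estimate as modelling the change with baseline adjustment. An independent t-test on the change would also be valid.
- Name one rank-based between-group test, such as Mann-Whitney, as a sensitivity analysis to be reported whatever the distribution looks like.
- Delete the transformation sentence for the primary and secondary outcomes.
- Confine the signed-rank test to within-group description, and say that it carries no claim of efficacy.

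This costs a few sentences. Trial conduct is unaffected, and the sample size stays at 37 per group before dropout and 100 in total, because it already assumes a two-sample comparison of means.

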**Methods:**

This randomized, double-blind, placebo-controlled trial will be performed at two centers and will include a *Banha-sasim-tang *group and placebo group. Each group will consist of 50 FD patients. Six weeks of administration of *Banha-sasim-tang *or placebo will be conducted. During the subsequent 2 months, follow-up observations of primary and secondary outcomes will be performed. The primary outcomes are differences as measured on the gastrointestinal symptom scale, and the secondary outcomes are differences as measured on the visual analogue scale for dyspepsia and on the questionnaire for FD-related quality of life. All outcomes will be measured at baseline, at 2, 4, and 6 weeks of treatment, and at the 1 and 2 month follow-up. Cutaneous electrogastrography will be performed and assessed at baseline and at 6 weeks.

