**Discussion:**

This trial will provide evidence of the safety and efficacy of *Banha-sasim-tang *for the treatment for FD. Furthermore, based on the assessment of the relationship between cutaneous electrogastrography recordings and dyspeptic symptoms in this trial, the possibility of clinical applications of cutaneous electrogastrography in the treatment of FD will be elucidated.

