## Discussion

The current clinical study is a randomized, double-blind, placebo-controlled trial investigating the safety and efficacy of frequently used herbal formulas as part of the national project for studying the traditional herbal medicines of South Korea. This clinical trial belongs to the 2009 Traditional Korean Medicine R&D projects funded by the Ministry for Health & Welfare & Family Affairs, Republic of Korea. BST is one of the most frequently prescribed herbal formulas in Korea, BST is thought to be safe, and experimental evidences support BST's effectiveness for dyspepsia [18-20]. However, there have not been any randomized controlled trials showing the effectiveness of BST for the treatment of FD. Through the current study, we expect to gain objective clinical evidences of the efficacy and safety of BST for the treatment of FD.

The causes of functional dyspepsia are diverse and overlapping. Of the putative causes of FD, delayed gastric emptying/gastric dysmotility is one of the most important causes of FD in Korea and has been reported to closely correlate to GMA recorded by cutaneous EGG [5]. Because many researchers have suggested that cutaneous EGG could be a relatively easy technique that can be used to assess GMA in clinical settings and EGG recordings showed a significant correlation with dyspeptic symptoms in FD patients and changes in cutaneous EGG parameters in FD patients could reflect changes in their gastric motility and their dyspeptic symptoms [29,30], it is postulated that a significant correlation can be found between dyspeptic symptoms of FD patients and cutaneous EGG recordings in this trial, and the improvement in dyspeptic symptoms after the oral administration of BST may be assessed by measuring the changes in cutaneous EGG parameters. Correlations in these parameters can evaluate the possibility of clinical applications of cutaneous EGG in the treatment of FD, and a detailed guide, based on biological evidences, for treatment in FD patients.

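### The only named analysis of adverse events is a significance test at 50 per arm, which for uncommon events cannot support the promised evidence on safety

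*Protocol article*

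**What the plan says.** The protocol article makes three statements about what the trial will show on safety:

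- Abstract, Discussion: "This trial will provide evidence of the safety and efficacy of" BST.
- Methods, Safety: "we will also assess whether 6 weeks of BST administration in FD patients is safe by above tests or CRF documentations". The tests meant are blood counts, liver and kidney chemistry, erythrocyte sedimentation rate and electrocardiogram, before randomization and after treatment. The section also lists reactions from the official product guide: pseudoaldosteronism, myopathy, skin disorders, liver malfunction, pneumonia and dry mouth. It gives no frequencies.
- Discussion: "we expect to gain objective clinical evidences of the efficacy and safety of BST for the treatment of FD".

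On analysis, the Statistical analysis section says "Adverse events will be calculated and compared using" a chi-square or Fisher's exact test. It names no method for the laboratory or ECG results. The sample size rests on the GIS total alone, "assuming Δ = 3.5 and σ = 5.37". The abstract's Methods state: "Each group will consist of 50 FD patients".

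**The concern.** The aim and the named method do not fit. The null hypothesis of a chi-square or Fisher test is that the two arms have the same event rate. Rejecting it can show harm, but failing to reject it does not show that harm is absent or small. With 50 per arm and uncommon events, a non-significant result is likely even when BST raises the rate several-fold.

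The error would run in the unfavourable direction: a real excess could pass unremarked. The article describes the product as available over the counter, and some of the listed reactions are serious. A p-value alone would not tell a reader how large an excess remains compatible with the data, which is what a safety statement needs.

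**Working it through.** **Inputs**

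- 50 per arm (abstract, Methods). This is also the natural denominator under "All analyses in this study will be based on the intention-to-treat principle".
- Two-sided 5% level. The article states it for the primary hypothesis ("by means of a 2-sided test yielding a 5% significance level"); I assume that it also applies to adverse events.
- Event rates: none in the article. All pairs below are assumptions.

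**The plan's own figure**

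n per arm = 2(1.96 + 0.8416)² × 5.37² / 3.5² = 2 × 7.849 × 28.837 / 12.25 = 36.95, rounded up to 37. With 25% dropout, 37 / 0.75 = 49.3, rounded up to 50 per arm and 100 in total. The stated sample size reproduces. It contains no adverse-event input.

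**Probability that the adverse-event test is non-significant**

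Let X and Y be independent binomial counts with n = 50 and rates p₀ (placebo) and p₁ (BST). The miss rate is 1 − Σ P(X = x) P(Y = y) over all pairs (x, y) with two-sided p ≤ 0.05, by exact enumeration.

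| Placebo vs BST (assumed) | Ratio | Fisher | Chi-square, uncorrected |
|---|---|---|---|
| 2% vs 4% | 2 | 99% | 95% |
| 5% vs 10% | 2 | 94% | 86% |
| 2% vs 10% | 5 | 81% | 62% |
| 10% vs 20% | 2 | 81% | 70% |
| 5% vs 15% | 3 | 76% | 61% |
| 5% vs 20% | 4 | 49% | 34% |
| 10% vs 30% | 3 | 36% | 27% |
| 5% vs 25% | 5 | 25% | 15% |
| 30% vs 60% | 2 | 17% | 12% |
| 10% vs 50% | 5 | 0.6% | 0.3% |

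The continuity-corrected chi-square gave the same miss rates as Fisher for these pairs. Where expected counts are small (2% vs 10% gives 50 × 6% = 3 expected events per arm), Fisher would normally be chosen, so its column is the relevant one for uncommon events.

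**What single results would and would not show**

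- Five cases on BST, none on placebo: Fisher p = 2 × C(50,5) / C(100,5) = 2 × 2,118,760 / 75,287,520 = 0.056. The uncorrected chi-square is 100 × (5 × 50)² / (50 × 50 × 5 × 95) = 5.26, p = 0.022. The two named tests fall on opposite sides of 5%.
- 10/50 on BST, 5/50 on placebo: Fisher p = 0.26. The risk difference is 10 percentage points, Newcombe 95% CI −4.3 to +24.2. The p-value says only that nothing was shown; the interval says that an excess of up to 24 points is not excluded.
- No events in 50 BST patients: the exact one-sided 95% upper bound solves (1 − p)⁵⁰ = 0.05, so p = 1 − 0.05^(1/50) = 5.8%. Rates up to about 1 in 17 remain possible.

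**The case against.** The strongest reply is that the article nowhere says a non-significant test will count as safety. It says only that events will be compared. The Safety section ties the question of safety to laboratory tests, ECG and case report forms, not to the chi-square test. The test is a valid comparison of proportions, low power for adverse events is usual in a trial sized for efficacy, and intervals may be specified in a full protocol or analysis plan that is not shown.

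Much of this stands, and it rules out three stronger readings that a reader might infer:

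- *That the plan equates p > 0.05 with safety.* No section states such a rule; it is a risk of interpretation.
- *That any two- to five-fold excess would be missed in about 60–80% of trials.* That range fits only pairs such as 2% vs 10%, 5% vs 15% and 10% vs 20%. Over the pairs tabulated, the miss rate runs from under 1% to about 99%, and the article gives no rates with which to choose among them.
- *That the test is the only safety assessment.* It is the only named statistical analysis of safety, but laboratory, ECG and case report form data are also collected.

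What the reply does not remove is the mismatch on the page. The article chooses a method and promises a conclusion, and nothing it states leads from one to the other. Low power is a reason not to rest a safety statement on a significance test; it is not a reason to enlarge the trial.

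**Conclusion.** The point holds as a cheap improvement, not as a design error. The one named analysis of adverse events can detect large excesses of common events, but it cannot support a statement that BST is safe with respect to uncommon ones. For the three pairs 2% vs 10%, 5% vs 15% and 10% vs 20%, the miss rate is 76–81% with Fisher and 61–70% with the uncorrected chi-square.

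This rests on 50 analysed patients per arm, a two-sided 5% level for adverse events, and assumed event rates. That the serious listed reactions fall in the low-rate region is likewise an assumption, since the article gives no frequencies. The logical point, that non-rejection is not evidence of no excess, does not depend on the rates.

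**What to change.** In the Statistical analysis section, make estimation the main safety analysis:

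- Report the number of patients by arm with any adverse event and with each reaction listed in the Safety section.
- For each, give the BST-minus-placebo risk difference with a 95% CI, for example Newcombe's.
- Give the exact upper 95% bound on the event rate under BST, naming it as one-sided or two-sided.
- Keep the chi-square or Fisher p-value as a descriptive addition, and state that p > 0.05 is not evidence of safety.
- In the abstract, the Safety section and the Discussion, word the safety conclusion as the excess risk that the data exclude.

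The cost is a few table columns and a more modest safety claim. No patients, visits or tests are added.
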